**5.2 Methodology of the second phase (current project) study**

Phone contacts will be made with mothers / families to invite the children involved in the first phase of the trial and his younger brothers, when present, to participate in the second phase of the project and request that attend the Clinical Research of the Hospital de Clínicas de Porto Alegre in pre-defined date. Mothers / families who are not found by phone will be visited at home.

Data collection will take place at the Clinical Research Center of the Hospital de Clínicas de Porto Alegre or at home with semi-structured questionnaire to obtain information on the current socio-demographic characteristics and some aspects related to the frequency of children in school preschool or day care; food frequency questionnaire to investigate the consumption of food (the same applied in the first phase of the study) and anthropometric measurements of children.

For the anthropometric measurements of children, will be taken two weight measures with the child barefoot wearing light clothing, positioned in the center of the scale (portable electronic scale with capacity of up to 200kg and sensitivity 50g), upright and distributed weight on both feet; and two height measurements with the barefoot child, standing upright, positioned in the center of the product, with arms extended along the body and the head up, looking at a fixed point at eye level. The heels, shoulders and buttocks should be flat on the stadiometer and internal bones of heels must touch as well as the inside of the knees, and feet must be united making a right angle to the legs. Will be calculated body mass index (BMI = weight [kg] / height2) and for the classification of children as the BMI / age and height / age will be used the new curves and WHO parameters35-37.

Data collection and anthropometric measurements will be performed by three students graduate, which will remain blinded to the groups they belong to children and their siblings (experimental or control).

The data collected will be stored by double entry, using the Excel program. For statistical analysis, SPSS for Windows is used.

Statistical analyzes will be based on the principle of "intention to treat". Initially, key features will be compared of patients lost to follow-up on those who are evaluated to rule out possible selection bias. The following comparisons of preschool and younger children in the intervention group with the control group will be made:

- Anthropometric indicators (BMI, height) using mean z scores nutritional classification of children.
- Eating habits, using the data to be obtained from the food frequency questionnaire. You may also be compared to the adequacy of diet in the first year of life with current.
- Following the 10 steps of healthy eating for children 2-10 years using the data to be obtained from the food frequency questionnaire.
- Adequacy of macro and micronutrients intake as recommended for the age group (Dietary Reference Intakes - DRIs).
- Total duration of breastfeeding (preschoolers only), using medians.
- Duration of EBF, prevalence of BF and adoption of healthy complementary feeding in the first year of life (for the younger siblings of preschoolers).

To quantify the impact of the intervention in different outcomes, the hazard ratios (HR) and 95% confidence intervals will be calculated by means of Cox regression. In the analyzes, will be considered cohabitation with the grandmothers and other relevant characteristics . Will be adopted p <0.05 as level of statistical significance.

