**1. ABSTRACT**

In view of the low breastfeeding rates (BF) and practical sub-optimal complementary feeding in Brazil; the large number of adolescent mothers in our country; the presumed influence of grandmothers on feeding practices of their grandchildren; the fact that adolescent mothers who live with their mothers (maternal grandmothers of children) are considered to have an increased risk of inadequate feeding practices of their young children; and also the lack of intervention studies with adolescent mothers and grandmothers, it was conducted in the years 2006 to 2008, a randomized clinical trial to evaluate the efficacy of an intervention (six BF counseling sessions and healthy complementary feeding, carried out in the first four months of the child's life, the first in the maternity and the others in households) directed to adolescent mothers and grandmothers on exclusive breastfeeding prevalence (EBF) in the first six months of life and the BF prevalence and adoption of healthy complementary feeding and timely in the first year of life. Due to the favorable results of the intervention on all outcomes studied, it is intended, with this study, knowing the impact of the intervention on dietary habits and nutritional status of children in preschool age and brothers who are born after the intervention. For this, 252 children who were part of the clinical trial will be reassessed at age 4-6 years and younger siblings. Children in the intervention group will be compared with the control group regarding: anthropometric indicators (BMI, height), diet, adequacy of intake of macro and micronutrients as recommended for the age group (Dietary Reference Intakes - DRIs), the duration of BF (preschool for only), the duration of EBF and BF prevalences in the first year of life (only for younger siblings). To quantify the impact of the intervention in the various outcomes will be used Cox regression (hazard-ratio). In the analyzes, will be considered cohabitation with the grandmothers and other relevant variables. Our hypothesis is that the positive impact of the intervention acquired in the first year of life has positively reflected in anthropometric indicators and eating habits of children in preschool and younger siblings.

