- The intervention reduced the unnecessary use of water and / or teas in children breastfed for the first six months by 52% (HR = 0.48, 95% CI 0.31 to 0.76) when it was applied only to adolescent mothers. When the intervention included maternal grandmothers, the protection was 47% (HR = 0.53; CI 95% = 0.35-0.80); and postponed for 44 days the use of these liquids in the group where only the adolescents received the intervention (78 days, 95% CI 50.2 to 105.8 without intervention versus 122 days, 95% CI 107.6 to 136.3 with intervention) and 67 days in the group where the grandmothers were also included in the intervention (63 days, 95% CI 47.2 to 78.7 without intervention versus 130 days, 95% CI 113.4 to 146.6 with intervention29.
- The intervention increased the median duration of EBF in 67 days in the group that only adolescent mothers received the intervention (103 days; 95% CI = 82.4 to 123.5 with intervention versus 36 days; 95% CI = 21.5 to 50 5 without intervention) and 46 days in the group where the grandmothers were also included in the intervention (89 days, 95% CI 56.8 to 121.2 with intervention versus 43 days, 95% CI 29.9 to 56.1 without intervention); and reduced by 48% the EBF abandonment in the first half when applied only to adolescent mothers (HR = 0.52; 95% CI = 0.36-0.76) and 36% when included maternal grandmothers (HR = 0,64, 95% CI = 0.46-0.90)30.
- The probability of a child be fed with another milk remained lower over the first six months of life in the group receiving the intervention. The median age of introduction of other types of milk was 95 days (95% CI 78.7 to 111.3) in the control group and 153 days (95% CI 114.6 to 191.4) in the intervention group. Therefore, the intervention delayed in nearly two months the introduction of other milks31.
- The intervention had a positive impact on the early introduction of complementary foods. At four months, 41% (95% CI 32.8 to 49.2) of the control group were receiving complementary foods. This prevalence decreased to 22.8% (95% CI 15.9 to 29.7) in the intervention group. However, the six-month prevalence rates of children receiving complementary foods were similar in both groups: 88.4% (95% CI 82.9 to 93.9) for the control group and 87.1% (95% CI 81,4 to 92.8) in the intervention group31.

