**5.1. Information about the first phase of clinical trial**

For sample size determination, the EpiInfo software was used with the following parameters: α = 5%; β = 20%; ratio between exposed and unexposed = 1: 1; prevalence of EBF in the first month in the group not exposed to the intervention = 56% (ALMEIDA, 1999); difference in the prevalence of EBF in the first month of the unexposed group and the group exposed to the intervention = 25 percentage points. Considering also the same difference between groups (25%) in reducing excess weight in the intervention group of preschool age (KOLETZKO, 2009), it was estimated minimum sample 48 mother-child pairs for each group. Added to this number 10% for losses and 20% for performing multiple regression analysis, totaling approximately 63 participants in each group.

Adolescent mothers, their infants and grandmothers were recruited in the rooming-in facility of the Porto Alegre University Hospital between May 2006 and January 2008, and followed in their homes to children reaching one year of age. Daily, including weekends, mothers were identified that met the following inclusion criteria: age under 20 years, living in the city of Porto Alegre, with healthy babies and birth weight equal to or greater than 2,500 g who had started breastfeeding. Mothers of twins and that, for mother or baby's problems could not stay in rooming and the adolescent mothers living with their mothers in law were not included in the study.

Once identified, mothers were classified into two groups: those who lived and not lived with their mothers (maternal grandmothers of the child). Next, by lottery, they were allocated to the control group (who did not receive the intervention) or the intervention group. In these, when mother and grandmother lived together, both were subjected to intervention; when not cohabiting, only the mother received the intervention. The inclusion of the latter group aimed to evaluate how much of the impact of the intervention could be attributed only to the adolescent mother. All mothers, regardless of the group to which they were allocated, received standard hospital care.

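### Younger siblings are compared by the mother's arm under the same intention-to-treat statement as the index children, with no allowance for shared mothers or for siblings being a post-randomisation subset

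*Protocol*

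**What the plan says.** - **Unit allocated.** Section 5.1 describes mothers classified by whether they lived with the maternal grandmother. It continues: "Next, by lottery, they were allocated to the control group (who did not receive the intervention) or the intervention group". The trial therefore randomised mothers, each with one index child.
- **Who the siblings are.** The Abstract speaks of "children in preschool age and brothers who are born after the intervention". Section 5.2 will "invite the children involved in the first phase of the trial and his younger brothers, when present". No number of siblings is given, overall or per mother.
- **What is compared.** Section 5.2 adopts intention to treat for the statistical analyses and then says "The following comparisons of preschool and younger children in the intervention group with the control group will be made". In the list that follows, total breastfeeding duration is restricted to preschoolers, and one item is restricted to siblings: "Duration of EBF, prevalence of BF and adoption of healthy complementary feeding in the first year of life (for the younger siblings of preschoolers"). Anthropometry, eating habits and nutrient adequacy carry no restriction, and section 3.2 names both sets of children for these.
- **How.** The same section fixes Cox regression, hazard ratios with 95% confidence intervals and p<0.05. It names cohabitation with grandmothers and other relevant characteristics as what the analyses will consider. The mother is not mentioned as a cluster.
- **Selection check.** The only one planned compares participants lost to follow-up with those evaluated.
- **Weight.** The Hypothesis section lists sibling breastfeeding and eating habits along with the main outcomes.

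**The concern.** Two separate problems can arise, and they act differently.

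**Shared mothers.** Children of one mother share her arm, her home and much of their diet. If more than one of them enters a model that treats children as independent, the standard error is too small, the interval too narrow and the false-positive rate above 5%.

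**Selection after randomisation.** Having a later child, how soon, and whether that child is brought to the visit are all settled after allocation. Randomisation balances mothers. It does not guarantee balance among the mothers who went on to have another child. The first phase changed these mothers' feeding behaviour: section 2 reports that "The intervention increased the median duration of EBF in 67 days" where only the adolescent mother was counselled (103 against 36 days), and by 46 days where grandmothers were included (89 against 43). An effect on spacing or further childbearing is conceivable. If there were one, the estimate itself would be biased, and wider intervals would not cure that.

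At stake is a prominent claim: that counselling given around one child carries over to the next.

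**Working it through.** **The plan's own figure.** There is none for siblings. The only sample-size calculation (section 5.1) counts mother-child pairs: 48 per group, raised by 10% and 20%, which is 48 × 1.1 × 1.2 = 63.4, or about 63. Four groups of 63 make the 252 index children. Siblings are not in that count.

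**Could a mother have two later children?** Recruitment ran from May 2006 to January 2008, and data collection was scheduled for July 2012 to April 2013. The interval from index birth to visit runs from about 4.5 years (January 2008 to July 2012) to about 6.9 years (May 2006 to April 2013). That leaves room for more than one.

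**Effect of ignoring shared mothers**

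Inputs not in the protocol, and therefore assumed: the within-mother correlation (ICC), the share of mothers with two siblings, and the share of index children with a sibling.

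Formulas, with m the number of children a mother contributes to one model:
- design effect DE = 1 + ICC × (Σm²/Σm − 1)
- actual two-sided error of a nominal 5% test = 2 × [1 − Φ(1.96/√DE)]

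This is the standard approximation when all children of a mother are in one arm. For a Cox model it is a guide, not an exact result.

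*Siblings modelled alone, 30% of sibling-mothers with two:*
- Σm²/Σm = (0.3 × 4 + 0.7 × 1)/(0.3 × 2 + 0.7 × 1) = 1.9/1.3 = 1.462
- ICC 0.3: DE = 1 + 0.3 × 0.462 = 1.138; 1.96/√1.138 = 1.837; error 6.6%
- ICC 0.5: DE = 1 + 0.5 × 0.462 = 1.231; 1.96/√1.231 = 1.767; error 7.7%
- The correct interval on the log hazard-ratio scale is wider by √DE, a factor of 1.067 to 1.109.

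*Range around these values:*

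| Case | Assumptions | DE | Actual error |
|---|---|---|---|
| Siblings alone, one per mother | any ICC | 1.00 | 5.0% |
| Siblings alone | 10–30% of sibling-mothers with two; ICC 0.1–0.7 | 1.02–1.32 | 5.2–8.8% |
| Index and sibling pooled | 20–50% of index children with one sibling; ICC 0.1–0.7 | 1.03–1.47 | 5.4–10.6% |

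The last row applies only if the two sets are put in one model.

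**Selection.** No figure can be given, because the protocol reports nothing on later births by arm. What can be checked is whether the planned comparison would show a difference. A mother whose index child is examined but who has no later child counts as evaluated. So does one who brings the index child but not the sibling. Comparing lost with evaluated participants therefore says nothing about whether the arms differ in who contributes a sibling, at what birth interval, or at what age.

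**The case against.** The strongest reply has four parts.

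1. **Independence is inferred from silence.** The protocol never says siblings are treated as independent. A robust variance, a frailty term or a limit of one sibling per mother could stand in an analysis plan that is not available here. This is fair, and it rules out calling the analysis wrong. It does not remove the point, because the protocol itself fixes the comparison, the model and the intention-to-treat label, and none of these distinguishes siblings from index children.
2. **Sharing a mother with the index child is harmless if the sets are modelled separately.** This stands. Several outcomes are assigned to one set only, and for the shared outcomes pooling is one reading, not the plain one.
3. **Siblings inherit a randomised arm.** True of their mothers as randomised. Comparing siblings by that arm respects the allocation, and bias needs an effect of the intervention on who had or brought a later child.
4. **The size rests wholly on assumptions.** This also stands.

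A reader might infer that the sibling p-values and intervals are wrong, or that the error rate reaches 11%. The documents support neither. With one sibling per mother and separate models the error stays at 5%. The 11% needs pooling, an ICC of 0.5 and a sibling from every family, which sits badly with inviting siblings only when there are any. A reader might also infer that longer breastfeeding changed birth spacing or further childbearing; the protocol gives no data on either.

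**Conclusion.** The point holds as a gap in the stated analysis that should be closed, not as a demonstrated error.

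- **Precision:** run as written, the sibling intervals are too narrow if any mother contributes more than one child to a model. The inflation is modest: about 6.6% to 7.7% for a nominal 5% test under the central assumptions (ICC 0.3 to 0.5, 30% of sibling-mothers with two siblings), and nil with one sibling per mother and separate models.
- **Validity:** the sibling comparison is made in a subset formed after randomisation, which intention to treat does not by itself protect. Whether it is biased, and by how much, is unknown, and the planned check would not show it.

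**What to change.** - State that index children and siblings are modelled separately; if they are combined for any outcome, cluster on mother.
- For siblings, use mother-clustered robust standard errors. Taking one sibling per mother, chosen by a fixed rule, would also restore the 5% level but discards data.
- Report by arm the number of mothers with a later child, the birth interval and the sibling's age at visit.
- Present sibling results as a comparison in a post-randomisation subset, and keep the full intention-to-treat claim for the index children.

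The cost is a few sentences of analysis text and one descriptive table, provided sibling birth dates are recorded. No further participants are needed. The downside is slightly wider intervals and a softer claim for siblings.

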**4. HYPOTHESIS**

Our hypothesis is that the positive impact of the intervention in the EBF and BF indicators and the adoption of healthy complementary feeding in the first year of life has positively reflected in anthropometric indicators and eating habits of children in preschool and their younger siblings.

To test this hypothesis, children who participated in the first phase of the trial will be evaluated at age 4-7 years and younger siblings, when present, the main outcomes: BMI, height, eating habits and appropriate consumption of macro and micronutrients, as well as total time of BF of the children involved in the first phase of the trial and prevalence and patterns of breastfeeding and eating habits of younger siblings.

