Data collection was performed at different times. In maternity ward, adolescent mothers and grandmothers, after agreeing to participate and signed the written informed consent, were interviewed separately to obtain sociodemographic data and aspects related to prenatal care, childbirth and experience prior to breastfeeding. Separate questionnaires were used for mothers and grandmothers. Information on the children's diets in the first six months of life were obtained monthly by telephone interview with the mother, or home visits in telephone contact impossibility. Interviewers were blind to the group to which they belonged mothers. To check the quality of information, were randomly selected 5% of mothers every month, which were submitted by the researcher coordinator of field, a second interview containing some key questions of follow-up questionnaire.

Intervention sessions occurred in the maternity ward and at home. In the maternity ward, occurred the first counseling session on breastfeeding according to the principles of the World Health Organization33, conducted by one of the team members formed by two nurses, a nutritionist and a pediatrician, all with extensive experience in BF, three consultants lactating by the International Board of lactation Consultant Examiners (IBLCE). Interventions in maternity ward were individual and performed separately for the mother and grandmother. In households, the advice was simultaneous.

In counseling sessions, professional, mother and grandmothers dialogued informally about various aspects related to breastfeeding - its importance and recommended duration; Factors that influence the production of milk; breastfeeding technique; pacifier use consequences; crying baby and communication - as well as specific questions for each mother and grandmother were clarified. The mothers were encouraged to breastfeed during the intervention, whenever possible, taking advantage of the opportunity to observe the feeding and guide as to positioning and latch.

As support material, flip charts specially designed for research were used containing information about breastfeeding and prevention and management of common problems. A handbook with similar content to the flipchart was distributed at the end of counseling at the hospital.

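### Total breastfeeding duration reads as a comparison of re-assessed children only; phase-1 weaning data for children not re-found are not brought in

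*Protocol*

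**What the plan says.** Section 4 (Hypothesis) names the target: "total time of BF of the children involved in the first phase of the trial".

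Section 5.2 begins its analysis text with "Statistical analyzes will be based on the principle of" intention to treat. The next sentence gives the only step for children who are not re-found: "key features will be compared of patients lost to follow-up on those who are evaluated to rule out possible selection bias". The list of comparisons follows, and for this outcome it reads "Total duration of breastfeeding (preschoolers only), using medians". After the list, the effect on the different outcomes is to be quantified: "the hazard ratios (HR) and 95% confidence intervals will be calculated by means of Cox regression".

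On the earlier phase, section 5.1 says that children were "followed in their homes to children reaching one year of age". It also says "Information on the children's diets in the first six months of life were obtained monthly by telephone interview with the mother", but gives no collection schedule for months 6 to 12. Section 2 (Introduction) reports breastfeeding proportions at 12 months and hazard ratios for weaning in the first 12 months, so weaning was tracked over that year.

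In section 5.2 the eating-habits item foresees a possible comparison with first-year diet. The breastfeeding-duration item mentions no first-year data, and the list of data to be collected does not name breastfeeding duration.

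**The concern.** BMI or current diet can be known only for a child who is seen again. Total breastfeeding duration is different, because much of it was observed before phase 2 began. A child not re-found should have either a weaning age in the first year on file or a record of still being breastfed at the last contact. If only re-assessed children are analysed, that information goes unused. The comparison then depends on who can be traced four to seven years later, and not on the randomised cohort that the hypothesis and the intention-to-treat statement point to. Comparing the features of lost and evaluated children can reveal selective loss but cannot correct it.

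This is separate from recall error. It concerns which children enter the analysis.

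**Working it through.** **Does the text fix the analysis set?** No sentence says that the comparison is confined to re-assessed children, and none says that phase-1 times are used for the others. The order in section 5.2 (lost versus evaluated, then the comparisons) points to evaluated children. Section 4 and intention to treat point to all children.

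**How much of the outcome did phase 1 observe?** Section 2 gives 38% and 62% breastfed at 12 months in the two groups not living with the grandmother, and 41% and 49% in the two that did. Weaned by 12 months: 62%, 38%, 59% and 51%, mean 52.5% with equal weights. The labels for the 38% and 62% look reversed against the hazard ratio of 0.51 (0.38^0.51 = 0.61), but the mean is unaffected. In three of the four groups fewer than half were still breastfed at 12 months (49% only just), so their medians lie at or below 12 months, within phase-1 follow-up.

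**Precision.** Inputs: 252 children (section 4, Methods), 1:1 allocation, and every re-assessed child weaned by then (assumption). The only loss allowance in the protocol is 10%, from the phase-1 sample size in section 5.1; the higher rates are assumptions. With E re-assessed children and M not re-found, the added events are 0.525 × M. Since SE(log HR) is about 2/√events, the width ratio is √(E / (E + 0.525M)). Power is Φ(√(events/4) × |ln HR| − 1.96), here at the phase-1 hazard ratio of 0.74 for the cohabiting groups.

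| Loss | E | M | Added events | Width ratio | Power, E only | Power, with added events |
|---|---|---|---|---|---|---|
| 10% | 226.8 | 25.2 | 13.2 | 0.972 | 62.1% | 64.5% |
| 20% | 201.6 | 50.4 | 26.5 | 0.940 | 57.1% | 62.3% |
| 30% | 176.4 | 75.6 | 39.7 | 0.904 | 51.6% | 60.0% |
| 40% | 151.2 | 100.8 | 52.9 | 0.861 | 45.7% | 57.6% |

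At a hazard ratio of 0.51, power is 98.5% or more in every row either way. These figures ignore the cohabitation strata and carry the 12-month hazard ratios over to total duration.

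**Selective re-contact.** Simulation: exponential weaning, 126 children per arm, 38% breastfed at 12 months, so λ = −ln(0.38)/12 = 0.0806 per month and the true median is ln 2/0.0806 = 8.6 months.

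| Loss pattern | Re-assessed-only median | Kaplan-Meier median with phase-1 times |
|---|---|---|
| 20% at random | 8.6 | 8.7 |
| 30% of those weaned before 12 months, 10% of others | 10.1 | 8.8 |
| 10% of those weaned before 12 months, 30% of others | 7.6 | 8.7 |

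A closed-form check agrees. In the second row the retained share is 0.62 × 0.7 + 0.38 × 0.9 = 0.776. Its median solves 0.7F = 0.388, so F = 0.554 and t = 10.0. In the third row the share is 0.62 × 0.9 + 0.38 × 0.7 = 0.824, so 0.9F = 0.412, F = 0.458 and t = 7.6.

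These shifts are in one arm's median. If an arm with 62% breastfed at 12 months (true median 17.4) has the same loss pattern, its re-assessed-only median becomes 19.8 or 15.0. The difference between arms then moves from 8.8 months to 9.7 (19.81 − 10.10) or 7.4 (15.04 − 7.62). With phase-1 times it is 8.8 or 8.9.

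**The case against.** A reader might infer that the plan discards phase-1 weaning ages, or that comparing medians is itself the fault. Neither is supported.

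- No sentence drops the phase-1 data. The restriction to preschoolers in the item separates index children from younger siblings; it does not mean re-assessed children only.
- A Kaplan-Meier median can use censored times. Section 2 reports phase-1 medians alongside hazard ratios, and section 5.2 already plans Cox regression, which accepts censoring. Most of the remedy is therefore in the plan; only the analysis set and the entry of phase-1 times are new.
- Censoring rules and data linkage are often left to a statistical analysis plan, which may exist and is not shown. This stands against calling the silence an error. It does not remove the mismatch among what the protocol itself states: the target in section 4, intention to treat, and the lost-versus-evaluated step.
- At 10% loss the gain is about 3% in interval width. That stands. However, 10% was the phase-1 allowance, and no phase-2 rate is given.
- Families not reached by telephone are to be visited at home, which should limit selective loss. That stands too, though it does not guarantee its absence.
- Weaning to 12 months has already been analysed, so the added events are not new findings. True, but the first year is part of total duration. A re-assessed-only analysis would reuse those events for some children and omit them for the rest.

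**Conclusion.** The point holds as an inexpensive improvement and does not invalidate the plan. Sections 4 and 5.2 leave open whether children not re-found contribute to total breastfeeding duration, and the most natural reading is that they do not. Because about half of the children were weaned within phase-1 follow-up, they can.

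The precision gain is small at 10% loss (about 3%) and moderate, 6% to 14%, at an assumed 20% to 40%. The stronger reason is protection against selective re-contact. The size of that benefit is illustrative: the loss patterns are assumed, and the simulation favours the remedy because loss depends only on weaning before 12 months, which phase 1 is taken to record in full. If re-contact also depends on duration beyond 12 months, censoring at the last phase-1 contact does not remove the bias.

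**What to change.** In section 5.2, replace the breastfeeding-duration item with a statement that total duration is analysed as time to event in all randomised children, using Kaplan-Meier medians and the already planned Cox model, taking account of cohabitation. Specify that:

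- weaning ages up to 12 months come from the phase-1 record where available;
- children not re-found and not known to be weaned are censored at their last phase-1 contact;
- phase-2 reports are used only for weaning after 12 months;
- medians in re-assessed children alone are shown as a sensitivity analysis.

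The cost is a change of analysis wording and linkage of the phase-1 file, with no new data collection for this purpose. Two limits should be stated: the analysis assumes that censoring at last contact is non-informative, and the precision of weaning ages between 6 and 12 months is unknown because section 5.1 gives no schedule for that window.
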